### Randomization, allocation, blinding, and confidentiality

A randomization sequence has been generated using Randomization.org in blocks of four to either group 1 – inspiratory muscle training with 40 % of maximal inspiratory pressure – or group 2 – sham inspiratory muscle training. An independent person not involved in this study possesses the computer-generated randomization sequence. A research assistant not involved in participant assessment obtains the code and sets the load in each device, according to randomization. A black tape hides the loading spring from the participant and from the investigators assessing outcomes.

There are no foreseen circumstances when un-blinding is permissible. When data collection is completed, the person responsible for the randomization list will provide assignment information to the investigators. Patient’s forms and other data sources are kept in a locked cabinet. Data are anonymized when entered into the database to protect confidentiality. Only investigators formally associated with the project will have access to the final study database.

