### Study design

This is a double-blind, parallel-group, sham-controlled randomized clinical trial. Participants are randomly assigned to receive inspiratory muscle training with a load equivalent to 40 % of maximum inspiratory pressure or inspiratory muscle training sham (no load) for 8 weeks. The study flowchart is depicted in Fig. 1. Participants are followed on weekly visits. Study outcomes are assessed at the end of the eighth week. The study timeline is summarized in Additional file 1: Figure S1, where detailed information on methods of assessment and protocols can be found.

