### Studied variables and methods of assessment

Participants are assessed as described in Additional file 1. Briefly, baseline physical activity is quantified using the International Physical Activity Questionnaire long form [20]. Body mass index is calculated as mass (kg) divided by the square of the height (m) and categorized as recommended by the World Health Organization [21]. Ambulatory blood pressure monitoring is performed with Spacelabs 90207 devices (Redmond, WA, USA). The protocol includes blood pressure measurement every 15 min during the daytime (6 a.m. to 10 p.m.) and every 20 min during the nighttime (10 p.m. to 6 a.m.) [22]. Functional capacity is assessed during exercise through O_2_ and CO_2_ expiration fraction in a metabolic system. Maximum oxygen consumption in each breath is recorded in ml/(Kg/min) [23, 24].

Maximum inspiratory and maximum expiratory pressure serve as indicators of inspiratory and expiratory muscle strength, respectively. Maximum inspiratory and maximum expiratory pressure are assessed using a digital pressure manometer (MVD-300, Microhard System, Globalmed, Porto Alegre, Brazil) [25, 26].

Inspiratory muscle endurance is determined using the incremental test proposed by Martyn et al. [27] using the Powerbreathe Plus® system (London, UK). The test is stopped when the subject cannot open the inspiratory valve or desires to stop the test owing to respiratory exhaustion (quantified using the modified Borg scale).

Blood pressure variability, heart rate variability, and the cardiac vagal tone are assessed to evaluate autonomic cardiovascular control. Non-invasive continuous blood pressure curves, heart rate, and electrocardiogram tracing are obtained simultaneously at a frequency of 1000 Hz using a Biopac MP150 (Biopac, California, EUA). Data are registered in a computer with biologic signal conversion capabilities.

The muscle metaboreflex is the adaptive blood flow redistribution from the peripheral circulation into the vascular bed of metabolically active (exercised) muscles [28]. The metaboreflex intensity is inversely related to one’s fitness. Inspiratory muscle metaboreflex is assessed by causing diaphragmatic fatigue and detecting peripheral blood flow reduction [28, 29]. Monitored parameters include: oxygen saturation, carbon dioxide partial expiratory tension, mean arterial pressure, and venous occlusion plethysmography. A detailed protocol can be found in Additional file 1.

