### Data management and statistical analysis plan

Data recorded in printed forms are kept in locked cabinets. Information is entered on Microsoft Excel spreadsheets by one person and reviewed by another. Numeric continuous variables, including blood pressure in the primary outcome measures, will be described as mean ± standard deviation or as median (interquartile range). Comparison between groups will be performed using Student’s *t* test or the Mann–Whitney U test, depending on variable distribution. As a superiority trial, differences in autonomic cardiovascular control and metaboreflex between groups will be tested with two-sided repeated-measures ANOVA. Results will be analyzed as per intention-to-treat. Participants who drop out and do not complete outcome assessment will be compared with those who completed the protocol but their data will be excluded from analysis. Statistical significance will be considered for *P* < 0.05. All analyses will be performed using PASW Statistics 18® (International Business Machines Corp., New York, NY).

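### Treatment assignments go to the investigators when data collection ends, with no requirement that signal processing, data review and the choice of test be settled first

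*Protocol article*

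**What the plan says.** The protocol article, under Randomization, allocation, blinding, and confidentiality, rules out earlier unblinding ("There are no foreseen circumstances when un-blinding is permissible") and then sets the trigger: "When data collection is completed, the person responsible for the randomization list will provide assignment information to the investigators". The same section mentions a final study database but does not tie release to it. During the trial, masking covers participants and outcome assessors: "A black tape hides the loading spring from the participant and from the investigators assessing outcomes". The Study design section gives the label: "This is a double-blind, parallel-group, sham-controlled randomized clinical trial".

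Three kinds of work described elsewhere bear on this trigger:

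- **Signals** (Studied variables and methods of assessment). Continuous blood pressure, heart rate and ECG are sampled at 1000 Hz, and "Data are registered in a computer with biologic signal conversion capabilities". Venous occlusion plethysmography is used for the metaboreflex. For further method the article points to a supplement: "A detailed protocol can be found in Additional file 1".
- **Data entry** (Data management and statistical analysis plan). One person enters the data and another reviews the entries.
- **Test choice** (same section). Groups are compared by Student's t test or Mann–Whitney, "depending on variable distribution", with blood pressure named among the continuous variables. No criterion is given. Participants who drop out without outcome assessment are left out of the analysis.

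**The concern.** Outcome data are not final when the last participant's measurements are taken. Raw recordings must be cleaned and turned into indices, entries checked, unusable readings set aside and a test picked. If those who do this know the arms, their judgement can be steered, knowingly or not, and nothing in the results would show it.

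The recipients are described only as the investigators. The same section uses that word for those who assess outcomes, and no separate masked analyst is mentioned. At stake are mainly heart rate variability, blood pressure variability, autonomic control and the inspiratory metaboreflex. The Discussion presents the metaboreflex assessment as a strength of the trial. The test choice reaches further, because it also covers the co-primary blood pressure comparison.

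**Working it through.** The point rests on order rather than on a figure, so the steps are set against the trigger first.

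| Step | Could it be finished before release? | Does the text require that? |
|---|---|---|
| Reduction of continuous blood pressure, ECG and plethysmography recordings | Yes, if data collection is read to include it | No |
| Second-person review of entered data | Yes | No |
| Decisions on unusable readings or recordings | Yes | Not addressed |
| Exclusion of participants without outcome assessment | Yes; the rule is stated in advance | The rule itself leaves little to judge |
| t test or Mann–Whitney, by distribution | Only once the data exist | No; no criterion is given |

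The last row is the firmest. A choice that depends on the observed distribution cannot precede the end of data collection, so under the stated trigger it can be made with assignments in hand.

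**How exposed are the 24 h means?** "Ambulatory blood pressure monitoring is performed with Spacelabs 90207 devices", every 15 min from 6 a.m. to 10 p.m. and every 20 min from 10 p.m. to 6 a.m. The inputs for scale come from Sample size calculation: difference 8 mmHg, SD 10 mmHg, 26 per group. That size reproduces. The normal approximation is n = 2(1.96 + 0.84)² × 10²/8² = 24.5, so 25; the t-based solution is 25.5, so 26 (two-sided 5%, power 80%).

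- Scheduled readings per participant: 16 h × 4 + 8 h × 3 = 64 + 24 = 88.
- Dropping one reading 20 mmHg from a participant's mean (assumed unweighted over 88) moves that mean by 20/87 = 0.23 mmHg. The mean of a 26-person arm moves by 0.23/26 = 0.009 mmHg.
- Dropping a whole recording whose 24 h value lies 2 SD (20 mmHg) from the arm mean moves that arm mean by 20/25 = 0.8 mmHg. One such removal in each arm, in opposite directions, moves the difference by 1.6 mmHg, which is 1.6/8 = one fifth of the planned effect.

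Editing single readings is therefore negligible. Rejecting whole recordings would not be, if it happened selectively. These are illustrations of scale under an assumed deviation, not estimates of bias. The documents give nothing comparable for the signal-derived outcomes.

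**The case against.** The strongest reply is that the order of steps is inferred. The article does not place signal processing after unblinding. Data collection can fairly include reading the tracings, since they yield outcome values only once read. Additional file 1 and any full analysis plan are not shown, and artefact rules, lock procedure and a test criterion commonly live there. This stands against any claim that these steps will be done unblinded. It does not remove the point, because the article itself names a trigger for release, and that trigger carries no condition.

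Three stronger readings are tempting and are not supported:

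- **That the trial is not truly double-blind.** Participants and assessors are masked through data collection, and the person who sets the load takes no part in assessment. No blinded analyst is claimed. Release afterwards does not contradict the label.
- **That dropouts can be chosen after unblinding.** The participant-level rule is fixed in advance, and whether outcome assessment was completed is largely a matter of fact. Only unusable readings or recordings remain open.
- **That unblinding inflates the type I error by a known amount.** Always taking the smaller of the t test and Mann–Whitney P values under the null, with 26 per arm, gave about 5.9% (normal data) to 6.7% (assumed lognormal, sigma 0.5) in 10,000 simulated trials; a fixed normality pre-test gave 5.2% to 5.4%. This measures an unfixed test, not unblinding. Two-sided P values do not change when A and B are swapped, so a person holding only masked codes could make the same choice.

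It is also fair that automated 24 h means leave little room for operator judgement.

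**Conclusion.** The point holds in a permissive sense. Release is tied to the end of data collection, and the text does not require that data review, signal reduction, decisions on unusable recordings and the choice of test be settled first. The exposure lies mainly in the signal-derived secondary outcomes and the data-dependent test choice, and less in the co-primary 24 h means.

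No numerical bias can be attached to it. The conclusion assumes that no unseen document already imposes the missing conditions; if one does, the article should say so. It is a weakness in a stated rule that is worth correcting while the trial is still enrolling. It is not evidence that any result will be biased.

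**What to change.** Change the trigger in Randomization, allocation, blinding, and confidentiality. The independent list holder releases a group code, masked as A/B, only when all of the following are done:

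1. Processing of the continuous recordings and plethysmography is completed blind.
2. Review of entered data is completed.
3. Unusable readings and recordings are listed with reasons.
4. The primary test is fixed without reference to group, either named now or chosen by a written criterion applied to data without group codes.
5. The database is locked.

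Which code is the active arm is revealed only after the primary analysis has been run.

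Step 4 must precede release of any code, because masking the labels alone does not stop a choice between two P values. The A/B mask is also the weaker safeguard, since a marked group difference in inspiratory muscle strength could suggest which arm is which. Finishing the judgement steps before any code is released does most of the work.

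The cost is a reworded rule in the protocol and a short delay before the arms are known. The list holder already exists, so no extra staff are needed.

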### Studied variables and methods of assessment

Participants are assessed as described in Additional file 1. Briefly, baseline physical activity is quantified using the International Physical Activity Questionnaire long form [20]. Body mass index is calculated as mass (kg) divided by the square of the height (m) and categorized as recommended by the World Health Organization [21]. Ambulatory blood pressure monitoring is performed with Spacelabs 90207 devices (Redmond, WA, USA). The protocol includes blood pressure measurement every 15 min during the daytime (6 a.m. to 10 p.m.) and every 20 min during the nighttime (10 p.m. to 6 a.m.) [22]. Functional capacity is assessed during exercise through O_2_ and CO_2_ expiration fraction in a metabolic system. Maximum oxygen consumption in each breath is recorded in ml/(Kg/min) [23, 24].

Maximum inspiratory and maximum expiratory pressure serve as indicators of inspiratory and expiratory muscle strength, respectively. Maximum inspiratory and maximum expiratory pressure are assessed using a digital pressure manometer (MVD-300, Microhard System, Globalmed, Porto Alegre, Brazil) [25, 26].

Inspiratory muscle endurance is determined using the incremental test proposed by Martyn et al. [27] using the Powerbreathe Plus® system (London, UK). The test is stopped when the subject cannot open the inspiratory valve or desires to stop the test owing to respiratory exhaustion (quantified using the modified Borg scale).

Blood pressure variability, heart rate variability, and the cardiac vagal tone are assessed to evaluate autonomic cardiovascular control. Non-invasive continuous blood pressure curves, heart rate, and electrocardiogram tracing are obtained simultaneously at a frequency of 1000 Hz using a Biopac MP150 (Biopac, California, EUA). Data are registered in a computer with biologic signal conversion capabilities.

The muscle metaboreflex is the adaptive blood flow redistribution from the peripheral circulation into the vascular bed of metabolically active (exercised) muscles [28]. The metaboreflex intensity is inversely related to one’s fitness. Inspiratory muscle metaboreflex is assessed by causing diaphragmatic fatigue and detecting peripheral blood flow reduction [28, 29]. Monitored parameters include: oxygen saturation, carbon dioxide partial expiratory tension, mean arterial pressure, and venous occlusion plethysmography. A detailed protocol can be found in Additional file 1.

### Intervention

Participants are extensively instructed on how to perform home-based inspiratory muscle training assisted by a Power Breathe Plus® (London, UK) device. For participants’ safety, research staff are responsible for device hygiene before and after the intervention period. To perform the exercise training, subjects should be seated, obstruct the nose with a nasal clip, and breathe in and out through the mouthpiece. The goal is to keep diaphragmatic breathing at 10–15 respirations per minute for a total of 30 min per day, 7 days a week.

Participants receiving active inspiratory muscle training (intervention group) perform the exercises with a load equivalent to 40 % of maximal inspiratory pressure. Those receiving the sham intervention (the control group) follow the same instructions but have no load applied to the respiratory exercises. The sham intervention was chosen as comparator because it is the most similar intervention available. It allows for blinding of investigators and participants, and is not expected to reproduce the effects of loaded exercises.

The complete study protocol consists of 56 daily training sessions completed over 8 weeks. During the scheduled weekly visit to the study center, participants are questioned about possible discomforts associated with the intervention, which may include: headaches, nausea, intense muscle fatigue, muscle cramps, and chest pain. Respiratory muscle strength is then reassessed; inspiratory threshold loading is adjusted accordingly, keeping a 40 % maximum inspiratory load for the intervention group throughout the study. The staff member who receives information about treatment allocation and adjusts the load neither participates in any assessments nor communicates with participants.

Participants in both groups receive a journal to register date, time, duration of training session, and possible symptoms or discomforts associated to the intervention. This serves as a mean to stimulate and estimate adherence to intervention. Adherence to the protocol is also reinforced on weekly follow-up phone calls.

### Sample size calculation

Sample size was estimated based on a small randomized clinical trial on the effect of inspiratory muscle training on blood pressure of hypertensive subjects in Brazil [13]. That study found an 8 mmHg difference in systolic blood pressure between the active treatment and the control group (standard deviation, 10 mmHg). To detect this difference with power of 80 %, and assuming an alpha error of 5 %, the study should include 26 participants per group. We opted for a 20 % inflation of this number to account for loss of follow-up and consent withdrawal – therefore, a total of 60 participants will be included and assigned to either intervention or sham treatment.

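### A 20% inflation of 26 per group gives 63–64 participants, not the stated 60, which covers a loss of only about 13%

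*Protocol article*

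**What the plan says.** All the figures stand in one paragraph of the protocol article, Sample size calculation. The planning difference comes from a small earlier trial: "That study found an 8 mmHg difference in systolic blood pressure between the active treatment and the control group" ("standard deviation, 10 mmHg"). The target is given as "To detect this difference with power of 80" per cent, "assuming an alpha error of 5" per cent, and the result is that "the study should include 26 participants per group". The authors then report a 20% "inflation of this number to account for loss of follow-up and consent withdrawal" and conclude that "a total of 60 participants will be included and assigned to either intervention or sham treatment". The conclusion is presented as the consequence of the inflation.

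The section on data management and statistical analysis adds two relevant facts. Groups are to be compared by Student's t test, or by the Mann–Whitney test if the distribution requires it. Participants who drop out without outcome assessment are left out of the analysis.

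**The concern.** The three printed numbers (26 per group, 20%, 60 in total) cannot all be right. Under either usual meaning of a 20% allowance, the total should be a few participants larger than 60. Because participants without outcome data are excluded, the number of completers sets the power for the blood pressure comparison, and the allowance is the only protection of the 80% target. A reader who relies on the paragraph would believe that the trial can absorb more loss than it can. The Abstract and the Discussion both describe the trial as adequately sized, and this calculation is the only support given for that.

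**Working it through.** **Inputs.** From Sample size calculation: difference 8 mmHg, SD 10 mmHg, power 80%, alpha 5%, 26 per group, inflation 20%, total 60. From the analysis section: t test as the between-group comparison, dropouts excluded. Two assumptions are mine. The test is two-sided: the paragraph does not say so, and the only mention of sidedness is that the autonomic and metaboreflex outcomes "will be tested with two-sided repeated-measures ANOVA". Allocation is 1:1 with equal loss in both arms.

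**Step 1: reproduce the 26.** The standardised difference is 8/10 = 0.8. For a two-sample t test with n per group, the noncentrality is 0.8 × √(n/2) on 2n − 2 degrees of freedom.

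- Two-sided 5%, 80% power: n = 25.52, rounded up to 26. This matches the plan.
- One-sided 5%: n = 20.03. This does not match, which supports the two-sided reading.
- Power at 26 per group: noncentrality 0.8 × √13 = 2.88, power 80.7%.

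The base number is therefore sound, and the discrepancy lies in the inflation step.

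**Step 2: apply the 20%.**

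| Reading of 20% | Per group | Total from equal arms | Total if rounded once |
|---|---|---|---|
| Inflation factor 1.2 | 26 × 1.2 = 31.2 → 32 | 64 | 52 × 1.2 = 62.4 → 63 |
| Expected loss of 20% | 26/0.80 = 32.5 → 33 | 66 | 52/0.80 = 65 |
| As printed | 30 | 60 | 60 |

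Even rounding 62.4 down gives 62, not 60.

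**Step 3: what 60 delivers.**

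- Implied inflation: 60/52 − 1 = 15.4%.
- Loss that still leaves 26 per group: 1 − 52/60 = 13.3%, which is 8 of 60.

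**Step 4: power at the numbers retained from 60** (t test, 8 mmHg, SD 10, two-sided 5%).

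| Loss from 60 | Left per group | Power |
|---|---|---|
| None | 30 | 86.1% |
| 13.3% | 26 | 80.7% |
| 16.7% (= 1 − 1/1.2, offset by a factor of 1.2) | 25 | 79.1% |
| 20% | 24 | 77.4% |

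With 24 per group, the difference detectable with 80% power is 8.26 mmHg instead of 8.

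**The case against.** Four points can be made for the plan.

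- **No loss rate is stated.** The paragraph gives an inflation, not an expected loss of 20%. A reader might infer that the trial plans to lose 20%, will finish with 24 per group and so misses its power target. The document does not support that: a factor of 1.2 offsets a loss of 16.7%, which leaves 25 per group and 79.1%. This stands, and it is why both figures are given.
- **The 80% is attached to 26 per group.** That claim reproduces. With no loss, 60 participants give 86.1%, and the target holds up to 13.3% loss. No figure in the document suggests that losses will be larger. This also stands.
- **The total may come from a base of 25.** The normal approximation gives 24.5, rounded up to 25 per group, and 2 × 25 × 1.2 is exactly 60. By that approximation, power is 80.7% at 25 per group and 79.1% at 24, so the 1.2 reading would hold its target. This may explain where 60 came from, but it contradicts the printed 26, which is the figure that matches the planned t test.
- **The planning inputs are far less certain than this discrepancy.** The difference and the SD come from a very small trial: 13 participants according to the Background, 11 allocated according to the Discussion. That is true and limits how much weight a point or two of power deserves. It does not make the three printed numbers agree.

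**Conclusion.** The stated total is wrong as a consequence of the stated inflation. A 20% inflation of 26 per group requires 63–64 participants, or 65–66 if 20% is meant as the expected loss. Sixty is 3 to 6 short of that and is in fact a 15.4% inflation covering 13.3% loss.

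The consequence is small. At the loss that a 20% inflation should have absorbed, power is 79.1% or 77.4% according to the reading, which is about 1 to 3 points below 80%. If losses stay within 8 of 60, there is no shortfall at all. A reader might infer that the trial is underpowered; on the document's own inputs that goes too far. What fails is the statement of how much loss the sample size covers.

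These results rest on a two-sided 5% t test, equal arms, equal loss in both arms, and the plan's own 8 mmHg and SD 10. They concern systolic pressure only, since the paragraph gives no planning values for diastolic pressure.

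**What to change.** Keep 60, since the article reports that enrolment is under way, and make the text match it. Remove the statement of a 20% inflation and put in its place, for example:

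> *60 participants allow for about 13% loss at 80% power; power for 8 mmHg (SD 10, two-sided 5% t test) is about 79% with 25 per group and 77% with 24 per group.*

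It may be added that 24 per group can detect 8.3 mmHg with 80% power.

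The cost is one sentence and a slightly less favourable stated allowance. No procedure, visit or participant number changes.
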